### Power calculation

The number of participants required for this study has been calculated to detect the expected change in WEMWBS score between the baseline assessment (M0) and the end of the 3-month cycle (M3) calculated using the formula ((score M^*n* + 1^ – score M^*n*^)/((score M^*n* + 1^ + score M^*n*^)/2)) × 100. The expected difference between intervention and control group was estimated 5.2 ± 10.3 based on a previous study [21]. A free sample size calculator (http://www.sample-size.net/sample-size-means/) was used*.* The minimum number of participants to show an absolute difference between the 2 groups (i.e., intervention and control groups) with alpha = 5% and power = 90% is of 63 per group. Thus, the theoretical total number of participants for the study is 126. Anticipating an 18% rate of participant loss during the follow-up period, the total number of participants required is 150 (75 participants per group).

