Museums have designed their spaces to create participatory art-based activity programs that can be carried out in a pleasant environment [8, 17–20]. For instance, in 2015, the Montreal Museum of Fine Arts (MMFA) developed “Thursdays at the Museum,” which is a participatory art-based activity performed by older community dwellers who live in Montreal creating art in group settings. In 2018, the effects of this participatory art-based activity on the well-being, quality of life, and frailty (i.e., physical health) of older community dwellers were examined [21]. With a pre-post intervention, single arm, prospective, and longitudinal design, we showed that the MMFA’s participatory art-based activity improved the well-being, quality of life, and frailty of older community dwellers in Montreal. Each outcome’s improvement evolved differently over the 3-month cycle of weekly art-based activities. Well-being was greater at the end of each workshop when compared to the beginning, with a similar magnitude of change throughout the cycle. In contrast, quality of life improved gradually over the course of the cycle. Finally, when comparing the cycle’s end to its beginning, the proportion of vigorous participants was greater, whereas the proportion of mildly frail participants was smaller. A major limitation of our first study was its design, as the gold standard to examine the effects of an intervention is a RCT in parallel groups.

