#### Randomization

After the baseline assessment, participants are randomly allocated to intervention and control groups using block randomization with a 1:1 ratio. The randomization list is established with the N’Query randomization software by the project manager, who is the only person able to identify participants based on their code. All investigators are blind to randomization. The project manager is not involved in the recruitment nor the follow-up of participants. He conducts the randomization process and informs the participants of to which group they are assigned. Randomization is performed the week before the first workshop.

Furthermore, a subset of participants is offered a Fitbit Alta HR (Fitbit, Inc.; San Francisco, CA, USA) to record physiological measures (i.e., heart rate, daily step count, sleep duration, and its phases). The subset is limited to 30 intervention group and 30 control group participants, determined in a second randomization that keeps the subsets as similar as possible to control for selection bias. This second randomization adopts the process used during the first randomization and the same project manager oversees it to ensure that all investigators remain blind. After the second randomization is completed, the project manager in charge of randomization provides selected participants with a Fitbit device, an assessment schedule and instructions. The project manager also installs the Fitbit application on participants’ portable electronic devices and creates their individual accounts with coded usernames.

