### Data analysis

Analyses will be performed (1) with the intention to treat for all enrolled participants randomized into two groups (i.e., intervention versus control) and (2) per protocol (i.e., removing data from participants who were not compliant with the protocol) for participants who will be entirely assessed through an 83.3% (i.e., participants who attended 10 on 12 workshops) compliance to the intervention. Analyses will be done through the SPSS Software (version 23.0; SPSS, Inc., Chicago, IL). Missing data will be taken into account with regression imputation. Data will be imputed only if the percentage of participants with missing data is under 10%. The continuous variables’ distributions will be studied (mean, median, mode, minimum, maximum, confidence interval around mean, standard deviation). For the categorical variables, frequencies will be calculated. First, the participants’ baseline characteristics (age, sex, etc.) will be described for each group and compared (i.e., intervention versus control) using parametric and non-parametric tests according to variables’ distribution. Pearson’s chi-square tests (or Fisher’s exact tests) will be used for qualitative variables. For quantitative variables, the statistical tests used will be unpaired *t* tests or non-parametric Mann-Whitney *U* tests for comparing 2 groups, as appropriate.

Second, group comparisons of changes (i.e., ((score M^*n* + 1^ – score M^*n*^)/((score M^*n* + 1^ + score M^*n*^)/2)) × 100) in outcome values between M0 and M1, M0 and M2, M0 and M3, M0 and M9, and M0 and M15 will be performed using repeated measures tests as appropriate. The global significance limit will be set at 0.05 and all tests will be bilateral. In addition to this univariate analysis, a multivariate analysis will be performed to determine the effect of the intervention while adjusting for age, sex, number of medications taken daily, and CPQ score. These adjusted variables are covariates that may influence the relationship between outcome measures (i.e., well-being, quality of life, and frailty) and the participatory art-based activity intervention.

Third, to identify the outcomes with the highest magnitudes of change (i.e., greater effect attributable to the intervention), we will graph the mean difference of each outcome that is significantly different when comparing intervention group participants to those in the control group. Results will be presented as forest plots.

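### The stated 63 per group gives 80% power rather than the stated 90%, and 150 enrolled with 18% loss leaves 123, short of the 126 required

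*Protocol article*

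**What the plan says.** All of the sample-size reasoning is in the Power calculation section of the protocol article. The outcome is the percentage change in WEMWBS score from M0 to M3.

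- Effect: "The expected difference between intervention and control group was estimated 5.2 ± 10.3 based on a previous study".
- Result: the minimum number "with alpha = 5% and power = 90% is of 63 per group", so that "the theoretical total number of participants for the study is 126".
- Attrition: "Anticipating an 18% rate of participant loss during the follow-up period, the total number of participants required is 150", that is, 75 per group.

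Two other sections supply the remaining inputs. Under Randomization, participants are "randomly allocated to intervention and control groups using block randomization with a 1:1 ratio". Under Data analysis, "The global significance limit will be set at 0.05 and all tests will be bilateral".

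The Background describes the earlier study from which the effect is taken: "With a pre-post intervention, single arm, prospective, and longitudinal design".

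**The concern.** Every input to a standard two-sample calculation is given, so the result can be checked directly. A standardized difference of about 0.5 is well known to need a little over 60 per group for 80% power and a little over 80 per group for 90% power. A claim of 63 per group at 90% therefore looks like an 80% result carrying the wrong label.

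This figure justifies the trial's size for its primary outcome. If it is overstated, a null primary result would be read as coming from a trial with only a 10% chance of missing the design effect. The steering committee's remit also includes re-assessing power and deciding on continuation, and it would do so from a wrong starting point.

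Two further points in the paragraph needed checking: whether 150 enrolled leaves 126 after the stated loss, and whether a single-arm study can supply an intervention-control difference.

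**Working it through.** **Inputs.** Difference 5.2, SD 10.3, alpha 5%, stated power 90%, 63 per group, 18% loss and 150 enrolled (Power calculation); two-sided tests (Data analysis); 1:1 allocation (Randomization). The ±10.3 is read as the common SD of the percentage change in each group, which the article does not say outright.

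Standardized difference: d = 5.2 / 10.3 = 0.505, so d² = 0.2549.

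**Sample size.** Normal approximation, n per group = 2(z₁₋α/₂ + z₁₋β)² / d²:

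| Power | Calculation | Normal approximation | t-test (noncentral t) |
|---|---|---|---|
| 80% | 2(1.960 + 0.842)² / 0.2549 | 61.6, so 62 | 62.6, so **63** |
| 90% | 2(1.960 + 1.282)² / 0.2549 | 82.5, so 83 | 83.4, so **84** |

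The plan's 63 is reproduced exactly by the t-test at 80% power. At 90% the requirement is 166 to 168 evaluable in total, not 126.

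**Other readings tried at 90% power.** None gives 63 per group:

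- one-sided 5%: 68 (and one-sided testing is excluded by the article)
- one-sample or paired test: 44
- SD divided by √2: 42; SD multiplied by √2: 165
- rounding limits of the inputs (5.15 with 10.35, and 5.25 with 10.25): 85 and 81

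Using the final-analysis threshold of 0.0498 in place of 0.05 changes power by less than 0.1 percentage point.

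**Power actually available** (two-sided 5%, difference 5.2, SD 10.3):

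| Evaluable per group | How it arises | Power, normal | Power, t-test |
|---|---|---|---|
| 61.5 | 150 enrolled, 18% lost | 79.9% | 79.3% |
| 63 | stated requirement | 80.9% | 80.3% |
| 75 | all 150 evaluable | 87.1% | 86.7% |

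With 63 per group, the difference detectable with 90% power is about 6.0 by t-test (5.95 by the normal approximation: 10.3 × 3.242 / √31.5).

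**Attrition.** 150 × 0.82 = 123, which is 3 below 126. Reaching 126 after 18% loss needs 126 / 0.82 = 153.7, so 154. Enrolling 150 tolerates 1 − 126/150 = 16% loss. The stated 75 per group is what results from 63 × 1.18 = 74.3, rounded up: the mark-up was apparently multiplied by 1.18 instead of divided by 0.82.

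**Source of 5.2.** The Background says the earlier study had one arm, so it cannot have observed an intervention-control difference. If a single-arm change is used as the difference, controls are taken not to change. As an illustration, t-test power at 63 per group is 58% for a true difference of 4 and 37% for 3. These two values are assumptions, not figures from the article.

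**The case against.** The central mismatch has no good defence: two-sided testing is explicit and no plausible variant of the calculation returns 63 at 90%. The reasonable objections concern what surrounds it.

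- **Attrition is minor.** The shortfall is three people and about one point of power. That is correct, and alone it would not need to be fixed urgently. It is still an arithmetic slip in the paragraph that has to be rewritten anyway.
- **The 18% may cover the whole 15-month follow-up.** The primary outcome is measured at M3, so loss by then could be smaller. This is fair: 79% is the figure if the full 18% applies to the primary outcome. But the plan itself applies 18% to the number needed for that outcome.
- **The miss rate doubles only at about 63 evaluable per group.** Intention-to-treat analysis of all 150, with imputation permitted when under 10% have missing data, could bring power up to 86.7%. The miss rate then runs from about 13% (75 per group) to 21% (61.5 per group). This stands as a qualification, but 10% is not reached anywhere in that range, and 20% is the rate at the plan's own 63.
- **The derivation of 5.2 is not shown.** It could be something other than a simple within-group change, or already allow for change in controls. That is so; the article establishes only that the source was single arm. The difference cannot have been observed there, but how it was obtained is inference.
- **The error might lie in the inputs rather than the power.** Reaching 90% with 63 per group would need an SD of about 8.9 to 9.0, which the article nowhere gives. The exact match at 80% points to the power label.

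**Conclusion.** The concern holds. On the article's own inputs, 63 evaluable per group gives 80.3% power, about 10 points below the claim; 90% would need 84 per group. The type II error at the planned evaluable size is about 20% against a stated 10%, and full retention of all 150 still leaves it at about 13%. This misstatement is the material error and must be corrected.

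The attrition figure is also wrong, but small: 123 against 126, or 154 needed against 150 planned.

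The description of 5.2 as a between-group difference is not supported by a single-arm source, so the design rests on an unstated assumption about change in controls.

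The conclusion assumes that 10.3 is the common SD within groups, a reading supported by the exact reproduction of 63 at 80% power.

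**What to change.** Rewrite the Power calculation section so that its figures agree:

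1. State that 63 evaluable per group gives 80% power, two-sided 5%, for a difference of 5.2 with SD 10.3, and say that 10.3 is the common within-group SD. If the authors believe an input rather than the power was misreported, they should give the corrected input and show the calculation.
2. State that 150 enrolled allows 16% loss before falling below 126, and that power is about 79% if 18% are lost by M3.
3. Explain how 5.2 was derived from the single-arm study. If it is that study's within-group change, say that it assumes no change in controls.
4. Give power at 63 per group for smaller differences alongside the design value, for example 37% for 3, 58% for 4 and 80% for 5.2.

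The cost is wording only. Correcting the statement needs no change in sample size or procedures, though the stated power becomes less favourable. Keeping the 90% claim instead would require 84 evaluable per group, which at 18% loss is 84 / 0.82 = 102.4, so 103 enrolled per group.

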### Data analysis

Analyses will be performed (1) with the intention to treat for all enrolled participants randomized into two groups (i.e., intervention versus control) and (2) per protocol (i.e., removing data from participants who were not compliant with the protocol) for participants who will be entirely assessed through an 83.3% (i.e., participants who attended 10 on 12 workshops) compliance to the intervention. Analyses will be done through the SPSS Software (version 23.0; SPSS, Inc., Chicago, IL). Missing data will be taken into account with regression imputation. Data will be imputed only if the percentage of participants with missing data is under 10%. The continuous variables’ distributions will be studied (mean, median, mode, minimum, maximum, confidence interval around mean, standard deviation). For the categorical variables, frequencies will be calculated. First, the participants’ baseline characteristics (age, sex, etc.) will be described for each group and compared (i.e., intervention versus control) using parametric and non-parametric tests according to variables’ distribution. Pearson’s chi-square tests (or Fisher’s exact tests) will be used for qualitative variables. For quantitative variables, the statistical tests used will be unpaired *t* tests or non-parametric Mann-Whitney *U* tests for comparing 2 groups, as appropriate.

Second, group comparisons of changes (i.e., ((score M^*n* + 1^ – score M^*n*^)/((score M^*n* + 1^ + score M^*n*^)/2)) × 100) in outcome values between M0 and M1, M0 and M2, M0 and M3, M0 and M9, and M0 and M15 will be performed using repeated measures tests as appropriate. The global significance limit will be set at 0.05 and all tests will be bilateral. In addition to this univariate analysis, a multivariate analysis will be performed to determine the effect of the intervention while adjusting for age, sex, number of medications taken daily, and CPQ score. These adjusted variables are covariates that may influence the relationship between outcome measures (i.e., well-being, quality of life, and frailty) and the participatory art-based activity intervention.

Third, to identify the outcomes with the highest magnitudes of change (i.e., greater effect attributable to the intervention), we will graph the mean difference of each outcome that is significantly different when comparing intervention group participants to those in the control group. Results will be presented as forest plots.

Fourth, analysis of compliance criteria will be based on between-group comparisons using, for quantitative variables, parametric and non-parametric tests according to variables’ distributions, and, for qualitative variables, Pearson Chi-square tests.

An intermediate analysis will be carried out with the first 90 participants. It will focus on the primary evaluation criterion and consider a *p* value < 0.001 sufficiently significant to stop the study.

The final analysis of the primary evaluation criterion in all 150 patients will consider the value *p* < 0.0498 as significant (Haybittle-Peto method).

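### Regression imputation, read as one predicted value per gap, either understates the standard error or shrinks the effect, modestly, when the 10% rule lets it operate

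*Protocol article*

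**What the plan says.** The Data analysis section plans an intention-to-treat analysis of everyone randomised, and a per-protocol analysis. For gaps in the data it says "Missing data will be taken into account with regression imputation". The next sentence limits this: "Data will be imputed only if the percentage of participants with missing data is under 10" per cent. It gives no number of imputed data sets, no pooling rule and no variance correction. On software it says "Analyses will be done through the SPSS Software", version 23.0, which does not settle which kind of imputation is meant.

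The same section states that "all tests will be bilateral". After one interim look, it takes p below 0.0498 in the final primary analysis "as significant (Haybittle-Peto method").

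The Power calculation section plans for a difference of 5.2 with SD 10.3 in the percentage change in WEMWBS from M0 to M3. It plans 75 participants per group after allowing for 18% loss during follow-up.

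**The concern.** A regression prediction is not an observation. It lies on the fitted line without individual scatter, and it carries the uncertainty of the fitted coefficients. A test that treats it as observed ignores both. What goes wrong depends on whether arm is a predictor:

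- **Arm included.** Each imputed value sits near its own arm's mean. The estimate is unbiased, but the sample looks larger and less variable than it is, so the standard error is too small.
- **Arm omitted.** Imputed values in both arms are drawn towards a common mean, so the estimated difference shrinks.

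At stake is the primary intention-to-treat result: either its p-value is somewhat too small, or its effect estimate is somewhat too small. The final threshold was lowered by 0.05 − 0.0498 = 0.0002 to pay for the interim look. An error of one to two and a half percentage points in the real level is much larger than that. The threshold itself is not in question here.

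**Working it through.** **Inputs from the protocol.** Difference 5.2, SD 10.3, 75 per group (Power calculation); two-sided tests and imputation only below 10% (Data analysis). The cap means at most 14 of 150: 14/150 = 9.3%, and 15/150 = 10.0% is no longer under 10%.

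**Assumptions not in the protocol.** Values missing at random; one predictor with correlation 0, 0.4 or 0.7 with the outcome, carrying none of the treatment effect; an unpaired comparison of the M0 to M3 change standing in for the planned repeated-measures test.

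**The plan's own figure.** n per group = 2 × (1.96 + 1.2816)² × (10.3/5.2)² = 2 × 10.51 × 3.923 = 82.5, so 83 for 90% power. The stated 63 gives about 80%. That is a separate matter; only the 5.2, the 10.3 and the 75 per group are used below.

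**Closed form, no useful predictor, missing share m.**

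- Arm included: each arm mean has true variance σ²/[n(1 − m)], while the reported variance is about σ²(1 − m)/n. The ratio of reported to true standard error is 1 − m. At m = 0.0933 this is 0.907, and the real level is 2 × [1 − Φ(1.96 × 0.907)] = 7.6%. At m = 0.05 it is 0.95, giving 6.3%.
- Arm omitted: the expected difference among imputed values is zero, so the effect is multiplied by 1 − m. This gives 5.2 × 0.907 = 4.7 at the cap and 5.2 × 0.95 = 4.9 at 5%.

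**Simulation.** 75 per arm, nominal 5% level, 15,000 trials under the null and 4,000 under the planned effect, one deterministic imputation:

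| Missing | Correlation | Arm in: SE ratio | Arm in: type I error | Arm out: type I error | Arm out: mean effect | Arm out: power |
|---|---|---|---|---|---|---|
| 5% | 0 | 0.94 | 6.2% | 4.9% | 4.95 | 85% |
| 5% | 0.4 | 0.95 | 6.1% | 5.2% | 4.90 | 84% |
| 5% | 0.7 | 0.98 | 5.2% | 5.2% | 4.96 | 85% |
| 9.3% | 0 | 0.91 | 7.5% | 4.8% | 4.72 | 84% |
| 9.3% | 0.4 | 0.92 | 7.1% | 5.1% | 4.73 | 83% |
| 9.3% | 0.7 | 0.95 | 6.3% | 5.1% | 4.70 | 81% |

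Power with complete data on 75 per group is 87%.

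**Variations.**

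- Adding one random residual to each prediction does not cure the problem. With arm included and 9.3% missing, type I error is 6.0% to 7.4%. With arm omitted, power is 79% to 80%.
- Further simulations at the 0.0498 level, arm included, gave 5.9% to 7.8% with 14 missing. With 7 missing they gave 6.0%, 5.4% and 5.2% for predictor R² of 0.1, 0.4 and 0.6. With 4 missing they gave 5.2% to 5.8%.
- If the predictor carries two thirds or all of the treatment effect, as M1 and M2 scores might, the effect with arm omitted and R² of 0.4 to 0.6 is 0.48 to 0.495 SD. Multiplied by 10.3, that is 4.9 to 5.1 points.

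**The remedy, tested.** Twenty imputations with arm in the model, pooled by Rubin's rules, at R² of 0.1 and 0.4: type I error 5.0% and 4.6%, SE ratio 0.99 to 1.01, mean effect 0.506 and 0.502 SD against a true 0.505. Power was 83% to 84%, against 82% to 83% for complete cases.

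**The case against.** Five things can be said for the plan.

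1. **The word single does not appear, and the composition of the imputation model commonly belongs in an analysis plan that is not shown.** This stands in part. Not listing the predictors is no fault. But the method is named, it is the only one named, and nothing suggests multiple imputation. If multiple imputation was intended, the sentence does not say so.
2. **With arm omitted, the test is valid.** This stands. A reader might infer that neither version gives a valid intention-to-treat test. The figures do not support that: the level stays at about 5%, and the fault is an attenuated estimate. Most of the power loss against 87% comes from the missing data themselves, since complete cases give only 82% to 83%.
3. **The inflation is small.** This stands in part. A reader might infer that the real error rate is well above 0.0498 whenever imputation is used. That needs arm in the model, missingness near the cap and a weak predictor.
4. **The shrinkage to 4.7 is a worst case.** This stands. WEMWBS is collected at M1 and M2 in both arms, and using those scores as predictors would recover much of the loss.
5. **The anticipated 18% loss exceeds the 10% limit, so imputation would be switched off.** This stands only if that much is missing from the data analysed. The 18% refers to the follow-up period, which the recruitment section puts at 15 months, while the primary endpoint is at month 3. Missingness there could fall below 10%, so it cannot be inferred that the fault will never arise, nor that it certainly will.

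**Conclusion.** The point holds at modest size. Read in its ordinary sense, the named method yields a standard error about 4% to 9% too small with 14 missing if arm is in the model, or an effect up to about 9% too small (5.2 to 4.7) if it is not. Neither outcome overturns the trial, and neither occurs if missingness at M3 reaches 10%. The result rests on reading the sentence as one predicted value per gap, on missingness at random, and on the assumed range of predictor strength. It is worth correcting because the weakness lies in a stated choice, operates inside the plan's own limit, and is removed by a method that held its level and recovered the planned effect in simulation.

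**What to change.** In the Data analysis section, replace regression imputation with one of the following:

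- **Multiple imputation** with 20 or more imputed sets, combined by Rubin's rules. The imputation model should contain arm, the M0 score, the other WEMWBS visits and the four adjustment covariates already listed (age, sex, number of daily medications, CPQ score).
- **A likelihood-based mixed model** on all observed visits, which suits the repeated-measures comparison already planned.

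The cost is one sentence, a little more analysis work, and confidence intervals slightly wider than single imputation with arm included would report. No change to the design or data collection is needed.

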**Methods/design:**

The current unicenter, randomized, clinical, controlled, comparative trial recruits 150 older community dwellers to two parallel arms (75 participants in the intervention group and 75 participants in the control group). The intervention is a 3-month cycle of weekly “Thursdays at the Museum,” which are structured 2-h-long art-based workshops performed in a group setting at the MMFA. The control group is composed of participants who do not take part in art-based activities, receive their usual health and/or social services, and commit to report any other activity practiced during the same time. Assessments of the primary outcome (well-being) and the secondary outcomes (quality of life, frailty, and physiological measures including heart rate, daily step count, sleep duration, and its phases) are performed on six occasions: at baseline, at the beginning of the second and third months, at the end of the third month, as well as 6 and 12 months after the last workshop. Statistical analyses are performed with the intention to treat and per protocol. Comparisons of changes in outcome measures between intervention and control groups use repeated measures tests.

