### Outcomes

The primary outcome is the change in WEMWBS score between the baseline assessment (M0) and the end of the 3-month cycle (M3), calculated using the formula ((score M^*n* + 1^ – score M^*n*^)/((score M^*n* + 1^ + score M^*n*^)/2)) × 100 [21, 26], expressed in percentage. Mean values and standard deviations will be used to define quantitative variables. The secondary outcomes are (1) the changes in WEMWBS scores between M0 and M1, M0 and M2, M0 and M9, and M0 and M15; (2) the mean WEMWBS scores before and after workshops in the intervention group at M0, M1, M2, and M3; (3) the changes in CESAM scores and its distribution of frailty categories (vigorous versus mild, moderate, and severe frailty) between M0 and M1, M0 and M2, M0 and M3, M0 and M9, and M0 and M15 [23]; (4) the change in EQ-5D scores, including VAS scores, between M0 and M1, M0 and M2, M0 and M3, M0 and M9, and M0 and M15 [25]; (5) the frequency of planned and unplanned physician visits, ER visits, and hospital admissions at M1, M2, M3, M9, and M15 [14, 16]; and (6) the changes in mean values of heart rate, daily steps, an sleep duration, and sleep phases, expressed in percentages, between M0 and M1, M0 and M2, and M0 and M3 for the subset of participants with recordings of these physiological measures. All changes will be expressed in percentages as mean values and standard deviations.

The number of workshops attended during the 3-month cycle of intervention is used to assess compliance with the participatory art-based activity. Compliance is defined as having attended at least 10 (83.3%) of the 12 workshops. If a participant attends a workshop for at least 1 h, they are considered to have attended a full workshop. If not, they are recorded as absent.

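### The primary outcome is a single arm difference at M3, but the stated test of changes spans five visits, and the term that decides the trial is not named

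*Protocol article*

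**What the plan says.** All references are to the protocol article.

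- **Outcomes.** "The primary outcome is the change in WEMWBS score between the baseline assessment (M0) and the end of the 3-month cycle (M3"), expressed as a symmetrised percentage. The other WEMWBS intervals, "the changes in WEMWBS scores between M0 and M1, M0 and M2, M0 and M9, and M0 and M15", are listed as secondary.
- **Power calculation.** The sample size rests on the arm difference in that same M0-M3 change: "The expected difference between intervention and control group was estimated 5.2 ± 10.3 based on a previous study". A calculator for two means was used, giving 63 per group.
- **Data analysis, second step.** The arms are compared on changes over five intervals by tests of the repeated-measures kind: "in outcome values between M0 and M1, M0 and M2, M0 and M3, M0 and M9, and M0 and M15 will be performed using repeated". The sentence closes with a qualifier that leaves the choice of test to what is appropriate. The Abstract (Methods/design) says the same without the qualifier: "Comparisons of changes in outcome measures between intervention and control groups use repeated measures tests".
- **Data analysis, first step.** Unpaired t and Mann-Whitney tests are named here, for comparing baseline characteristics.
- **Data analysis, end.** The interim on the first 90 participants concerns the primary criterion and may stop the study at p < 0.001. "The final analysis of the primary evaluation criterion in all 150 patients will consider the value" p < 0.0498 as significant. No test or model term is attached to either limit.

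**The concern.** The change formula reduces M0 and M3 to one number per participant. One number per person is not a repeated measure, so a repeated-measures test of changes needs at least one further interval, and Outcomes calls every other WEMWBS interval secondary. The two results that such an analysis usually reports first are the group main effect and the group-by-time interaction. On change scores, the main effect tests whether the arm difference averaged over M1, M2, M3, M9 and M15 is zero. The interaction tests whether that difference is the same at every visit. Neither null is a zero difference at M3.

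At stake is what decides the trial. A benefit at M3 could be called non-significant because it fades after the cycle (main effect) or because it is steady (interaction). A trial with no M3 benefit could be called positive because of differences elsewhere. With the term left open, the choice could also be made once results are known. These profiles are plausible here: the Background hypothesises that outcomes evolve differently over time and says only that benefit may persist after the workshops stop.

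**Working it through.** **Inputs.** From Power calculation: difference 5.2, SD 10.3, 63 per arm. From Data analysis: two-sided tests, final limit 0.0498. Assumed, because the article does not give them: SD 10.3 at every visit, equal correlation r between any two of the five changes, with r = 0.3, 0.5 or 0.7, and the effect profiles below.

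**The plan's own figure.** n per arm = 2 × (z_alpha/2 + z_power)² × (SD/difference)², with (10.3/5.2)² = 3.923.
- 90% power: 2 × (1.960 + 1.282)² × 3.923 = 82.5, so 83.
- 80% power: 2 × (1.960 + 0.842)² × 3.923 = 61.6, so 62 (63 with the t distribution).

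The stated 63 thus matches 80% power, not 90%. That is a separate matter; it is why the benchmark below is 80%.

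**M3 test.** SE = 10.3 × √(2/63) = 1.835. 5.2/1.835 = 2.83. Power = Φ(2.83 − 1.96) ≈ 81% (normal), about 80% with t. This does not depend on the other visits.

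**Group main effect.** SD of the mean of five changes = 10.3 × √((1 + 4r)/5), which is 6.83 at r = 0.3 and 8.98 at r = 0.7. SE = 1.217 and 1.600.
- Building to 5.2 at M3, gone by M9 (1.73, 3.47, 5.2, 0, 0): mean difference 10.4/5 = 2.08. 2.08/1.217 = 1.71 and 2.08/1.600 = 1.30, so power is about 40% and 25%.
- Steady 5.2: 5.2/1.217 = 4.27 and 5.2/1.600 = 3.25, so about 99% and 90%.
- 5.2 at M1 and M2 only, zero at M3: the mean difference is again 10.4/5 = 2.08. The main effect therefore rejects equally often whether the M3 difference is 5.2 (fading profile) or zero.

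**Group-by-time.** Its noncentrality is proportional to the sum of squared deviations of the five arm differences from their mean. For a steady effect that sum is zero, so the rejection rate equals alpha whatever the size of the benefit.

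**Simulation.** 20,000 trials per scenario and correlation, 63 per arm, alpha 0.0498; ranges are over r = 0.3 to 0.7.

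| Arm difference at M1, M2, M3, M9, M15 | M3 test | Group main effect | Group-by-time |
|---|---|---|---|
| 0, 0, 0, 0, 0 | 5% | 5% | 5% |
| 1.7, 3.5, 5.2, 0, 0 | 79-81% | 25-40% | 64-96% |
| 1.7, 3.5, 5.2, 2.6, 2.6 | 80% | 49-73% | 23-52% |
| 5.2 at all five | 80-81% | 90-99% | 5% |
| 0, 0, 5.2, 0, 0 | 80% | 10-14% | 67-97% |
| 5.2, 5.2, 0, 0, 0 | 5% | 25-39% | 86-100% |
| 0, 0, 0, 5.2, 5.2 | 5% | 25-39% | 86-100% |

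The hand calculations and the simulation agree. The omnibus terms are sometimes weaker and sometimes stronger than the M3 test. Only the M3 test follows the M3 difference alone.

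**The case against.** The strongest reply is that the article never specifies a single omnibus model. It lists the intervals one by one, speaks of tests in the plural, and ends with a qualifier that leaves room for judgement. One group comparison per interval, M0-M3 included, is a natural reading, and an M3 contrast from a mixed model over all visits is itself a repeated-measures analysis. The 0.001 and 0.0498 limits are tied to the primary criterion, which Outcomes defines as the M0-M3 change. The exact contrast may also be named in the full protocol or a SAP, neither of which is shown.

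Much of this stands. A reader might infer that the stated test certainly has the wrong null, that the sample size and the 0.0498 limit were set for a different test, or that the interim tests a different hypothesis from the final analysis. The article does not support those inferences, because an M3 contrast fits its wording. The interim and final hypotheses would diverge only if an omnibus term were used and the interim came before the M9 and M15 data.

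It does not dispose of the point. This is not just detail left to another document: the article does state a test for changes, and the usual terms of that test do not match its primary outcome or its sample size. The two-sample tests that would match appear only under the baseline comparison.

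**Conclusion.** The point holds in a limited form. The primary outcome and sample size concern one contrast; the stated analysis allows that contrast and at least two others with different nulls, and nothing says which is held against 0.001 and 0.0498.

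For a true M3 difference of 5.2, the group main effect could have as little as 25-40% power if the benefit is gone by M9, and the interaction 5% if it is steady, against about 80% for the M3 test. It would be wrong to infer that the omnibus terms always lose power: the main effect reaches about 90-99% under a steady effect. It would also be wrong to infer general type I error inflation: with no effect at any visit all three tests reject about 5% of the time. Rejection with a null M3 difference needs a real effect at another visit.

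The sizes depend on the assumed equal correlations of 0.3 to 0.7, a common SD of 10.3 and the chosen profiles. That the omnibus nulls differ from the M3 null depends on none of these.

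**What to change.** In Data analysis, state that the primary test is the between-arm difference in M0-M3 WEMWBS change. It may be a two-sample comparison of that change or the M3 group contrast from a mixed model over all visits; name one. Apply p < 0.001 at the interim and p < 0.0498 at the final analysis to that contrast only. Keep the omnibus group and group-by-time tests over M1 to M15 as secondary analyses of the profile over time, which suits the hypotheses on evolution and persistence in the Background. Align the Abstract sentence.

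The cost is a few words, with no new data and no more participants. The one thing given up is the omnibus result as a possible primary analysis, including its higher power should the benefit prove steady. The choice should be recorded before anyone sees results by arm.
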